### Interventions

2.7

All participants will receive basic treatment prior to intervention. Per the *Chinese Guidelines for Secondary Prevention of Ischemic Stroke and Transient Ischemic Attack* (21), this basic treatment includes three aspects: (1) Controlling risk factors such as blood pressure and blood glucose; (2) Administering regular-dose aspirin for antiplatelet aggregation (if no contraindications) and atorvastatin for lipid regulation and plaque stabilization; (3) Providing health education on diet, lifestyle, and physical activity. Participants in the acupuncture and sham acupuncture groups will receive a 3-week intervention: one 30-min session daily, 5 times weekly (2 rest days on weekends). The active drug group will take betahistine mesilate tablets orally three times daily for three consecutive weeks.

In the acupuncture group (Group A), participants will undergo acupuncture with filiform needles (Huatuo brand, Suzhou, China; Figure 2) at the following acupoints: Baihui (GV20), bilateral Fengchi (GB20), bilateral Wangu (GB12), and bilateral Taichong (LR3) (Figure 3; Table 2). After needling the acupoints, needles will be twisted 90–180° and lifted and inserted by 3–5 mm to induce a *deqi* sensation. This stimulation will be applied immediately after insertion and then repeated at 10-min intervals during the 30-min needle retention period, yielding three stimulation episodes per treatment session.

**Figure 2 fig2:**
[figure not shown]
Streitberger sham acupuncture device.

**Figure 3 fig3:**
[figure not shown]
Location of acupoints and non-acupoints.

**Table 2 tab2:** Location of acupoints and non-acupoints.

Acupoints and non-acupoints	Location
GV20 (Baihui)	On the head vertex, at the midpoint of the line connecting the two ear apices, 5 cun above the anterior hairline midpoint.
GB20 (Fengchi)	In the anterior region of the neck, inferior to the occipital bone, in the depression between the origins of sternocleidomastoid and the trapezius muscles.
GB12 (Wangu)	On the lateral head (posterior to the ear), in the depression inferior to the mastoid process at the sternocleidomastoid attachment.
LR3 (Taichong)	On the foot dorsum, 1 cun proximal to the 1st-2nd metatarsophalangeal joint, between the 1st and 2nd metatarsal bones.
Non-acupoint 1	1.5 cun lateral to GV20 (Baihui)
Non-acupoint 2	1 cun inferior to GB9 (Tianyou, on the lateral neck, posterior to the sternocleidomastoid muscle, at thyroid cartilage upper border level).
Non-acupoint 3	1.5 cun lateral to GB21 (Jianjing, on upper back, midpoint of C7 spinous process-acromion line, approximately 4 cun lateral to posterior midline).
Non-acupoint 4	1 cun superior to LR3 (Taichong).

In the sham acupuncture group (Group B), participants will receive treatment with retractable blunt needles (Streitberger type, Suzhou, China; Figure 2) at non-acupoints (Figure 3; Table 2), using skin-non-penetrating stimulation.

In the active drug group (Group C), participants will receive betahistine mesilate tablets (trade name: Minshilang).

### Outcome measures

2.8

#### Primary outcome

2.8.1

The primary outcome will be assessed using the DHI. The DHI yields a total score of 0–100, with three subscales: Physical (P, 28 points), Emotional (E, 36 points), and Functional (F, 36 points). A higher total score is indicative of greater functional impairment attributable to dizziness, whereas a lower score denotes less severe dizziness-related disability (Supplementary File 3).

#### Secondary outcomes

2.8.2

##### Dizziness and Anxiety Rating Scale (DARS)

2.8.2.1

This scale quantifies vertigo severity by rating standing balance dysfunction, gait balance impairment, current vertigo status, confusion or disorientation, and global impression of disease severity (as rated by both physicians and patients). Total scores range from 0 to 36, with higher scores indicating more severe vertigo (Supplementary File 4).

##### Vertigo diary

2.8.2.2

Participants will be instructed to record comprehensive details of each vertiginous episode in a vertigo diary, including episode frequency, onset and offset timestamps, vertigo Visual Analogue Scale (VAS) scores, and severity gradings. The diary will be completed manually by participants upon cessation of each episode and subject to regular monitoring by dedicated research personnel (Supplementary File 5).

##### 36-Item Short Form Health Survey (SF-36)

2.8.2.3

This scale includes domains of physical functioning, role-physical, bodily pain, role-emotional, mental health, vitality, social functioning, and general health. Higher scores indicate better quality of life (Supplementary File 6).

##### TCD

2.8.2.4

TCD will be used to monitor cerebral blood flow (CBF), as it is well-established for non-invasive intracranial hemodynamic assessment. Two clinically validated indices of CBF status will be measured: Mean Flow Velocity (MFV) and Resistance Index (RI). A standardized protocol will be applied to 9 target intracranial vessels, specifically the left middle cerebral artery (L-MCA), right middle cerebral artery (R-MCA), left anterior cerebral artery (L-ACA), right anterior cerebral artery (R-ACA), left posterior cerebral artery (L-PCA), right posterior cerebral artery (R-PCA), basilar artery (BA), left vertebral artery (L-VA), and right vertebral artery (R-VA).

##### fMRI data acquisition and scanning parameters

2.8.2.5

All fMRI data will be acquired using a 3.0 T GE Discovery 750 MRI scanner (Milwaukee, WI, USA) at the Affiliated Hospital of Chengdu University of Traditional Chinese Medicine. During scanning, participants’ heads will be immobilized with customized foam pads, and dedicated earplugs will be provided to minimize head motion artifacts and reduce noise.

Data acquisition will include axial structural imaging using a T1-weighted fast spoiled gradient echo (FSPGR) sequence, positioned perpendicular to the anterior commissure-posterior commissure (AC-PC) line, covering the entire brain from the vertex to the skull base. Parameters: repetition time (TR) = 7 ms, echo time (TE) = 3.1 ms, inversion time (TI) = 450 ms, field of view (FOV) = 240 mm × 240 mm, matrix = 256 × 256, slice thickness = 1.0 mm, flip angle = 15°, and scan time = 246 s. Resting-state fMRI (rs-fMRI) will be acquired using a single-shot gradient echo-planar imaging (GRE-EPI) sequence. Parameters: repetition time (TR) = 2000 ms, echo time (TE) = 30 ms, field of view (FOV) = 240 × 240 mm^2^, matrix = 64 × 64, slice thickness = 4.0 mm, flip angle = 90°, and scan time = 300 s. Diffusion Tensor Imaging (DTI) will be acquired using a whole-brain diffusion-weighted single-shot spin-echo EPI sequence. Parameters: repetition time (TR) = 6,800 ms, echo time (TE) = 86.3 ms, field of view (FOV) = 256 × 256 mm^2^, matrix = 120 × 120, slice thickness = 3.0 mm, flip angle = 90°, scan time = 224 s.

##### Expectation Rating Scale (ERS)

2.8.2.6

Participants in each group were asked, “What is your expected efficacy of the treatment for vascular vertigo?” with the following response options: “Excellent efficacy” (symptom improvement >75%); “Moderate efficacy” (symptom improvement 50–75%); “Slight efficacy” (symptom improvement 25–50%); and “No change” (symptom improvement 0–25%). “Excellent efficacy” was defined as high expectation, while the remaining options were defined as low expectation. This assessment was conducted at the time of at baseline. To minimize confounding factors, the same physician, who was blinded to the specific treatment allocation, performed the evaluation for all participants (Supplementary File 7).

#### Safety outcomes

2.8.3

Adverse events (AEs) include acupuncture-related events (bleeding, hematoma, pain, infection, syncope) and betahistine mesilate-related adverse reactions (gastrointestinal symptoms, rashes, other allergic responses). All AEs will be documented in detail on the Case Report Form (CRF) when they occur. For serious adverse events (SAEs—defined as death, life-threatening conditions, disability, or hospitalization), the principal investigator must report to the trial site and hospital ethics committees within 24 h, with accurate CRF documentation. All AEs will be followed up until resolution, and the ethics committee will determine whether to terminate the trial if necessary.

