### Design and setting

2.2

This is a multicenter, double-blind, randomized, controlled study that meets the recommendations of the Standard Protocol Project: Intervention Trials guidelines (19). This trial will be conducted in four clinical subcenters: the Affiliated Hospital of Chengdu University of Traditional Chinese Medicine, Chongqing Hospital of Traditional Chinese Medicine, Shuangliu District Hospital of Traditional Chinese Medicine in Chengdu, and Longquanyi District Hospital of Traditional Chinese Medicine in Chengdu. A total of 234 eligible participants will be randomly assigned to the active drug group, the acupuncture group, and the sham acupuncture group (1:1:1 allocation ratio). Participants will be evaluated at baseline, week 3, week 11, and week 23. Transcranial Doppler ultrasonography (TCD) and multimodal MRI will be performed at baseline and at week 3. All outcome assessors will be blinded to group assignment. The flowchart and results evaluation schedule of this trial are shown in Figure 1 and Table 1. The protocol was approved by the Medical Ethics Committee of the Affiliated Hospital of Chengdu University of Traditional Chinese Medicine (approval no. 2025KL-062) (Supplementary File 1) and is registered with the International Traditional Medicine Clinical Trial Registration Platform (registration no. ITMCTR2025001283).

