**Figure 1 fig1:**
[figure not shown]
Flowchart of the research procedure.

**Table 1 tab1:** Study schedule for data measurements.

Timepoint	Study period				
	Enrolment	Allocation	Treatment	Follow-up	
	Week-1	Week 0	Week 3	Week 11	Week 23
Enrolment					
Eligibility screen	×				
Informed consent	×				
Physical examination	×				
PMH and PTH	×				
CD or CM	×				
Randomization		×			
Interventions					
Group A (*n* = 78)		×	×		
Group B (*n* = 78)		×	×		
Group C (*n* = 78)		×	×		
Assessments					
DHI		×	×	×	×
DARS		×	×	×	×
Vertigo diary		×	×	×	×
SF-36		×	×	×	×
TCD		×	×		
fMRI parameters		×	×		
ERS		×			
Participants safety					
AE		×	×	×	×

*Group A, acupuncture group; Group B, sham acupuncture group; Group C, active drug group; PMH, past medical history; PTH, prior therapy history; CD, concomitant diseases; CM, concomitant medications; Group A, acupuncture group; Group B, sham acupuncture group; Group C, drug control group; DHI, Dizziness Handicap Inventory; DARS, Dizziness and Anxiety Rating Scale; SF-36, 36-Item Short Form Health Survey; TCD, transcranial Doppler ultrasonography; fMRI, functional magnetic resonance imaging; ERS, Expectation Rating Scale; AE, Adverse Event.

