#### Recruitment and informed consent

2.3.1

Participants will be recruited from the outpatient and inpatient departments of the Affiliated Hospital of Chengdu University of Traditional Chinese Medicine, Chongqing Hospital of Traditional Chinese Medicine, Chengdu Shuangliu District Hospital of Traditional Chinese Medicine, and Chengdu Longquanyi Hospital of Traditional Chinese Medicine. Recruitment is scheduled to commence on July 1, 2025. Investigators will strictly adhere to the inclusion and exclusion criteria to determine each individual’s eligibility for the study.

All potential participants will be informed of the study’s purpose and nature, and provided with comprehensive information about the research, including its procedures, potential benefits, and risks. Before enrollment, they will voluntarily sign an informed consent form (Supplementary File 2). Participants reserve the right to withdraw from the study at any time without penalty or loss of benefits, and are not required to provide a reason for withdrawal. Any reasons for withdrawal, if provided, will be documented.

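### Adverse events are recorded as they arise, but during treatment the needling arms have 15 sessions with staff and the drug arm has no described contact before week 3, so the acupuncture-versus-drug safety comparison is at risk of unequal ascertainment

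*Protocol article*

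**What the plan says.** Section 2.8.3 gives the recording rule: "All AEs will be documented in detail on the Case Report Form (CRF) when they occur". It describes the scope by treatment: "Adverse events (AEs) include acupuncture-related events (bleeding, hematoma, pain, infection, syncope) and betahistine mesilate-related adverse reactions", the latter being gastrointestinal symptoms, rashes and other allergic responses. Serious events go to the ethics committees within 24 hours.

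Section 2.7 sets the contact pattern. The acupuncture and sham groups have "one 30-min session daily, 5 times weekly (2 rest days on weekends") for three weeks. For the comparator, "The active drug group will take betahistine mesilate tablets orally three times daily for three consecutive weeks"; no treatment visit is described. Section 2.6 states that the acupuncture practitioners cannot be blinded.

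Section 2.2 sets the evaluations: "Participants will be evaluated at baseline, week 3, week 11, and week 23". Table 1 ("Study schedule for data measurements") has its own AE row, marked at weeks 0, 3, 11 and 23 and not split by arm.

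Two other passages bear on contact with the drug arm. Section 2.8.2.2 says that the vertigo diary is "subject to regular monitoring by dedicated research personnel", without limiting this to any arm. Section 2.3.1 says "Participants will be recruited from the outpatient and inpatient departments" of the four hospitals.

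Safety belongs to the first primary objective (section 2.1), in a sentence that compares all three arms. The abstract names the AE records as the source for the safety assessment.

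**The concern.** A rule that records events when they arise captures what somebody sees or what the patient volunteers. Its yield depends on how often patient and staff meet. Here that frequency is tied to the treatment arm during the three weeks in which treatment-related events are most likely to appear.

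A bruise or a faint at a needling session happens in front of a practitioner. A few days of stomach upset on tablets in the first week may be over by week 3, and then has to be remembered and reported. The listed drug reactions are partly of this transient kind. The staff present at the needling sessions also know the allocation.

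At stake is the comparison of acupuncture with betahistine on mild events. The likely direction is fewer recorded events in the drug arm, so that acupuncture looks worse by comparison and genuine mild drug reactions are understated. Differences in elicitation cannot be repaired at the analysis stage.

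**Working it through.** **The plan's own figure.** The article states no AE rate, no capture fraction and no sample size for safety, so there is no safety figure to reproduce. The only number borrowed from the sample-size section is the group size: 66 / 0.85 = 77.6, rounded up to 78 per group, and 3 × 78 = 234, as section 2.5 states.

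**Scheduled contacts after week 0 and before the week 3 visit.**

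| | Acupuncture | Sham | Drug | Source |
|---|---|---|---|---|
| Treatment sessions with staff | 5 × 3 = 15 | 5 × 3 = 15 | none described | 2.7 |
| Scheduled evaluations | 0 | 0 | 0 | 2.2, Table 1 |
| Diary monitoring | frequency not given | frequency not given | frequency not given | 2.8.2.2 |

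At weeks 3, 11 and 23 all arms have the same AE assessment in Table 1. The imbalance is therefore confined to the treatment period and comes from the 15 sessions. The two needling arms have equal contact, so contact frequency does not distort the comparison between them.

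**Illustration of what unequal capture would do (all rates assumed).** Let the true risk of a mild event be p in both arms, with capture fraction c_A under needling and c_D under drug.

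- Recorded risk = p × c
- Apparent risk ratio = (p × c_A) / (p × c_D) = c_A / c_D, which does not depend on p
- Expected recorded cases per arm = 78 × p × c

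With p = 0.20 and c_A = 0.95, the needling arm records 0.20 × 0.95 = 0.19, or 78 × 0.19 = 14.8 cases. For the drug arm:

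| c_D | Recorded risk, drug | Expected cases, drug | Apparent ratio | Chance of a nominally significant excess under needling |
|---|---|---|---|---|
| 0.95 | 0.19 | 14.8 | 1.00 | nominal |
| 0.80 | 0.16 | 12.5 | 0.95/0.80 = 1.19 | 7% |
| 0.60 | 0.12 | 9.4 | 0.95/0.60 = 1.58 | 23% |
| 0.40 | 0.08 | 6.2 | 0.95/0.40 = 2.38 | 52% |

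The last column uses a two-sided 5% normal-approximation test of two proportions with 78 per arm. It depends on p: at c_D = 0.60 it is 13% for p = 0.10 and 34% for p = 0.30. The plan does not announce such a test; the column only shows how the recorded data could mislead a reader who made one.

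With equal capture the ratio is 1.00, so the distortion comes entirely from the difference in capture. The true event profiles also differ by treatment (bleeding or syncope against stomach upset or rash), so a common p is a simplification.

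**The case against.** The strongest reply is that AE collection is not left to chance. Table 1 schedules an AE assessment at the same four times in every arm, so the as-they-occur rule is not the only one. The diary is monitored regularly in all arms, and inpatients on tablets also see hospital staff. Setting 15 sessions against no scheduled evaluation therefore compares treatment sessions with study visits; it does not count every contact, and the true number in the drug arm is unknown. A condensed article may also leave the method of AE elicitation to the full protocol or case report form. No specific acupuncture-versus-drug AE test is stated, and the likely direction works against acupuncture, so it would not manufacture a favourable safety claim for it.

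Much of this stands, and it limits the point. It does not remove it. A common week 3 visit does not equalise capture when two arms have already had 15 opportunities to add events to the same form. The diary is for vertigo episodes; neither its monitoring nor inpatient care is said to include an AE enquiry, and outpatients are recruited too. The point rests on the recording rule and the visit schedule that the article does state, not on a missing detail. If the full protocol already prescribes a uniform enquiry during weeks 0–3, what remains is a sentence to add to the article.

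A reader might go further and infer that the safety comparison is biased as a matter of fact, or that the between-arm AE table could not be interpreted. The documents do not support either. They show a mechanism and a likely direction, but no rates, and they provide common assessments that can carry a fair comparison.

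**Conclusion.** The stated recording rule and visit schedule together put the acupuncture-versus-drug AE comparison at risk of unequal ascertainment, most likely through under-recording of mild, transient events in the drug arm. The facts behind this are firm: 15 sessions in each needling arm, and no evaluation or treatment visit described for the drug arm between weeks 0 and 3. The size is not known. The apparent ratios of 1.19 to 2.38 rest on assumed capture of 95% against 80% to 40%, and the case counts also on an assumed 20% risk; they show scale and are not estimates for this trial.

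Serious events are less exposed because of their own reporting route. The sample size and the primary efficacy analysis are untouched. The change is worth making because safety is part of a primary objective and the remedy is cheap, but the weakness does not undermine the trial.

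**What to change.** State in section 2.8.3 that all three arms answer the same AE questions at the same times:

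- in weeks 1–3, a short weekly AE self-report on a page added to the existing vertigo diary;
- at the week 3, 11 and 23 visits, the same questions, covering the whole interval since the previous assessment.

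Base the comparison of acupuncture with drug on these commonly elicited events. Separately, report every AE in full for each arm, including those seen at needling sessions, and flag how each was detected (common questions, session observation, spontaneous report). Session-observed events must not be dropped: leaving out bleeding or syncope seen only at a session would hide genuine needling harms and could create the opposite bias.

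The cost is a slight extra burden on patients, one diary page and one extra table, with no new visits or staff. If recruitment began as scheduled in section 2.3.1, participants already past week 3 can contribute only what the common visits collected, and the report should say so.

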### Quality control

2.9

To ensure trial quality, the principal investigator will provide training to all study staff on operational procedures, outcome measures, and eligibility criteria. The principal investigator will also oversee the study to maintain data accuracy. Case Report Forms (CRFs) and study data will be securely stored, with key documents retained for 5 years post-publication. Any protocol deviations will be reported to the ethics committee, which will determine whether to modify or terminate the study.

### Statistical methods

2.10

#### Clinical data analysis

2.10.1

Clinical outcomes will be analyzed using SPSS 23.0 statistical software, with a significance level of *p*-value < 0.05. All analyses will be performed by independent statisticians blinded to group assignments and interventions. Two core analysis sets will be used: (1) Full Analysis Set (FAS): All randomly assigned participants who received at least one treatment session. Missing values for primary outcomes will be imputed using the Last Observation Carried Forward (LOCF) method, and FAS results will be the primary analytical basis. (2) Per Protocol Set (PPS): Participants with no exclusion criterion violations, ≥10 completed acupuncture sessions, and at least the Week 3 assessment. PPS results will serve as supplementary references. Relevant statistical analyses will also cover case distribution analysis, which will calculate the sample size of each analysis set per group, case distribution across study centers, and total numbers of dropouts and withdrawals (with respective reasons), and present these data in detailed tables.

The correlation between baseline treatment expectation and changes in DHI will be examined using Pearson correlation. In addition, multiple linear regression models will be constructed with change in DHI as the dependent variable, and baseline expectation score, treatment group, baseline DHI, age, and sex as independent variables, to examine whether expectation independently predicts treatment response. Exploratory interaction terms between treatment group and expectation will be tested to evaluate whether the magnitude of the acupuncture effect differs according to baseline expectation level.

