### Sample size

2.5

The sample size was calculated on the basis of the primary outcome, change in total DHI score. The assumed mean DHI scores were derived from a previous randomized trial on vestibular vertigo (20) and supported by a pilot study of 30 PSVV patients conducted by our team prior to this trial. The pilot data indicated a mean DHI reduction of approximately 12 points in the acupuncture group compared to sham, which informed our assumed group differences. On thess evidence, this study assumes that the mean Dizziness Handicap Inventory (DHI) score will be 21 in the acupuncture group for post-stroke vascular vertigo, 33 in the sham acupuncture group, and 30 in the active drug group, with a predefined standard deviation (SD) of 20. Sample size calculation will be performed using PASS software, with a set power (1-*β*) of 0.90 and a significance level (*α*) of 0.05. Following this calculation, a minimum of 66 participants will be required for each group, yielding a total sample size of 198; considering a 15% attrition rate, the total sample size will be adjusted to 234, with no fewer than 78 participants in each group.

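### LOCF as the primary handling of missing DHI can bias the arm contrast in either direction; the cost in power depends on how many participants are lost before week 3

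*Protocol article*

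**What the plan says.** Under Clinical data analysis (2.10.1), the Protocol article fixes the rule for missing DHI: "Missing values for primary outcomes will be imputed using the Last Observation Carried Forward (LOCF) method". The full analysis set (FAS) is defined as "All randomly assigned participants who received at least one treatment session", and "FAS results will be the primary analytical basis". The only other analysis is the per-protocol set, which requires the week 3 assessment: "PPS results will serve as supplementary references". No analysis under a different missing-data assumption is named.

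DHI is measured at baseline and at weeks 3, 11 and 23 (Design and setting; Table 1). Neither Sample size nor Primary outcome says which visit is primary.

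Sample size (2.5) sets the expected losses: "considering a 15% attrition rate, the total sample size will be adjusted to 234". The assumed means are given as "score will be 21 in the acupuncture group for post-stroke vascular vertigo" and "33 in the sham acupuncture group, and 30 in the active drug group", with SD 20, "with a set power (1-*β*) of 0.90 and a significance level (*α*) of 0.05".

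**The concern.** One treatment session is enough to enter the FAS, and no DHI is taken between baseline and week 3. A participant lost during treatment is therefore analysed with a score from before treatment began. A participant lost after week 3 keeps an earlier score to the end. The method assumes that nothing changes after the last observation, while the plan's own assumed means expect treatment to change the score. Entry from two weeks after stroke also makes some recovery plausible in every arm.

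Two things are at stake. First, the primary contrast can be wrong, and not reliably in the cautious direction. Dropout could well differ by arm: two arms attend 15 needling sessions and one takes tablets, and the blinding check covers only the needling arms. Second, the 15% inflation protects power if losses only reduce the number analysed. LOCF instead keeps the lost participants with stale values, which dilutes the effect. In addition, the filled-in values are analysed as if observed, so uncertainty about the missing outcomes is not carried into the result.

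This is a rule that the document states, not a detail left to an analysis plan.

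**Working it through.** **Inputs from the Protocol article.** Means 21, 33 and 30; SD 20; alpha 0.05; power 0.90; 66 evaluable and 78 randomised per arm; 15% attrition. **Assumptions, because the document gives no figure:** baseline DHI 40, 50 or 60; baseline–outcome correlation 0.5; the dropout splits; dropouts would have followed their arm's mean course.

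**1. The plan's own figure.** The grand mean is 28, and the squared deviations sum to 49 + 25 + 4 = 78. For a one-way F test, λ = n × 78/400. Power is 0.896 at n = 65 and 0.900 at n = 66, so 66 per arm reproduces. 66/0.85 = 77.6, hence 78 per arm and 234 in total. With 78 per arm and nothing lost, power is 0.944.

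**2. Bias.** Let d be an arm's dropout share and c the mean change missed after the last observation. The LOCF mean is the true mean minus d × c, so the acupuncture–sham contrast is shifted by d(sham) × c(sham) − d(acu) × c(acu). If baseline is carried forward and baseline is 50, c(acu) = 21 − 50 = −29 and c(sham) = 33 − 50 = −17. The true contrast is −12.

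| Dropout, acupuncture / sham | Shift | Contrast under LOCF |
|---|---|---|
| 15% / 15% | −2.55 + 4.35 = +1.8 | −10.2 |
| 20% / 10% | −1.7 + 5.8 = +4.1 | −7.9 |
| 10% / 20% | −3.4 + 2.9 = −0.5 | −12.5 |

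For baselines 40 to 60, the second row runs from −8.9 to −6.9 and the third from −11.5 to −13.5. The first row does not depend on baseline. Equal dropout is therefore not safe. Nor does unequal dropout always bias: at 10% acupuncture and 2.9/17 = 17.1% sham the shift is zero.

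**3. Power from dilution alone (SD kept at 20).** If a share q in every arm carries baseline forward, differences shrink by (1 − q) and λ = 78 × 78 × (1 − q)²/400.

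| q | F-test power, 78 per arm |
|---|---|
| 0 | 0.944 |
| 5% | 0.920 |
| 8.2% | 0.900 |
| 10% | 0.888 |
| 15% | 0.847 |

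At 15%, the 12- and 9-point differences become 10.2 and 7.65.

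**4. Power allowing for variance.** Mixing carried baselines with treated scores changes the spread. With 15% per arm carrying baseline forward and assumed baselines 40/50/60, power is 0.83/0.78/0.71 on final scores and 0.88/0.84/0.78 on change scores (SD of change 20).

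**5. Power if losses come later.** With baseline 50, 15% lost per arm, and a carried value that already holds 50%, 80% or 100% of the final mean change, power is 0.89, 0.93 or 0.94.

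**6. Type I error (two arms, 78 each, same improvement in both, all dropout before week 3, SD 20, correlation 0.5).** Bias = difference in dropout × improvement; rejection rates by simulation.

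| Assumed improvement | 5% vs 15%: bias, type I error | 5% vs 25%: bias, type I error |
|---|---|---|
| 5 points | 0.5, about 5% | 1.0, about 6% |
| 10 points | 1.0, about 6% | 2.0, about 9% |
| 20 points | 2.0, about 9% | 4.0, about 21% |

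**The case against.** The strongest reply is that the harm depends on facts the document does not give. The 85% figure needs the whole 15% to be lost before week 3. Follow-up runs to week 23, and a loss after week 3 carries a treated score; steps 3 and 5 show power still at or above 90% in many such patterns. Entry has a minimum time since stroke but no maximum, and requires persisting symptoms, so some participants may have stable scores and little missed change. With a small improvement, type I error stays close to nominal. All of this stands, and it is why the sizes are given as ranges.

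It is also said that safeguards exist: the per-protocol set leaves out those without a week 3 score, and dropouts will be tabulated with reasons. These make the problem visible. They do not correct the primary estimate, and omitting early leavers does not test the LOCF assumption.

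A reader might defend LOCF as conservative. Step 2 does not support that: with more loss under sham than acupuncture, the contrast can be inflated.

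**Conclusion.** The rule should be changed. LOCF governs the primary result and can bias the DHI contrast in either direction, by the between-arm difference in dropout share times change missed. Steps 3 to 6 give the size, which rests on the assumed baseline DHI, correlation, and timing and split of dropout.

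Three stronger readings are tempting and are not supported:

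- **That LOCF necessarily takes power below 90%.** From dilution alone this needs more than about 8% per arm to carry baseline forward. If sham loses more than acupuncture, power can exceed 90% because the effect is inflated.
- **That bias arises whenever dropout differs.** The condition is a difference in the product; it can be zero with unequal dropout and non-zero with equal dropout.
- **That LOCF explains low power for acupuncture against drug.** The 9-point difference has about 80% power at 78 per arm with no loss, about 73% with 66 completers, and about 66% with 15% carrying baseline forward. Of the 24-point gap to 90%, 90 − 73 = 17 come from sizing on the three-group test and 73 − 66 = 7 from LOCF.

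**What to change.** Replace LOCF as the primary method by one of these:

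- a likelihood-based repeated-measures model with baseline DHI in the outcome vector (baseline mean constrained equal across arms, arm-by-visit terms at weeks 3, 11 and 23); or
- multiple imputation by arm, using baseline and all observed visits.

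Baseline should not enter the model only as a covariate: participants lost before week 3 would then have no outcome row and would silently leave the FAS. Name the visit at which the primary contrast is read. Add one delta-adjusted or reference-based sensitivity analysis. Keep LOCF at most as a sensitivity analysis.

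If data are missing at random, 15% loss leaves at least the information in 78 × 0.85 = 66 completers per arm, so the F-test power returns to about 0.90 under the plan's own means and SD.

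The cost is a change of wording and modest extra programming on visits already scheduled; no new data are needed. The downside is reliance on missing-at-random, which the sensitivity analysis probes. The change should be made before any outcome is seen by arm.
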